### Sample size calculation

2.17

A sample size calculation for the PE RCT was conducted to assess the effect of the intervention on the primary outcome, the 6-Minute Walk Test (6MWT), while accounting for comorbidity status and any potential interaction between comorbidity and the intervention. The calculation was based on:

A two-way factorial design incorporating intervention group (PE vs. control) and comorbidity status (yes/no) as binary factors, with a binary outcome based on the 6MWT, reflecting whether participants achieved a clinically meaningful improvement.A logistic regression model including intervention, comorbidity, and their interaction term as covariates.

The null hypothesis (H_0_) of no treatment effect was tested against the alternative hypothesis (H_1_) as either a main effect of the intervention or a significant intervention–comorbidity interaction, using a chi-square test derived from the logistic regression model.

Assumptions for the calculation were as follows: in the control group, it was assumed that 40% of participants with comorbidity and 20% without comorbidity would fail to achieve a clinically meaningful improvement in 6MWT. In contrast, in the intervention group, these proportions were expected to be reduced to 10% and 20%, respectively. This corresponds to a relative risk of 0.5, which is considered clinically significant.

Based on 10,000 simulation runs, a total of 73 participants per combination of intervention and comorbidity status (i.e., 292 participants in total) would be required to achieve approximately 80% statistical power at a 5% significance level. The simulations were performed using R software, version 4.1.2.

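### The assumed intervention-group failure rates appear transposed: as printed they give relative risks of 0.25 and 1.0 and about 98% power, not 0.5 and 80%

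*Protocol article*

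**What the plan says.** Section 2.17 plans for a binary outcome, failure to reach a clinically meaningful improvement on the 6-minute walk test. Four equal cells are formed by intervention group and comorbidity status.

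- Control group: "40% of participants with comorbidity and 20% without comorbidity would fail to achieve a clinically meaningful improvement in 6MWT".
- Intervention group and summary of the effect: "these proportions were expected to be reduced to 10% and 20%, respectively. This corresponds to a relative risk of 0.5".
- Test: a chi-square test from a logistic model with intervention, comorbidity and their interaction. The alternative is an intervention effect or an interaction.
- Result, from 10,000 simulation runs: 73 per cell, 292 in total, "would be required to achieve approximately 80% statistical power at a 5% significance level".

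**The concern.** The section fixes the order of the two figures in each group: with comorbidity first, without comorbidity second. In that order the intervention takes failure from 40% to 10% in one stratum and from 20% to 20% in the other. The second pair is no reduction, and neither pair has a relative risk of 0.5.

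This is the only sample-size justification for the primary outcome, and the two possible readings describe different trials. As printed, all the benefit lies with participants who have comorbidity, and the half of the trial without it (150 planned, section 2.2) is assumed to gain nothing. That sits badly with the stated aim of benefit with and without comorbidity. With the figures exchanged, the benefit is a uniform halving of risk. Section 2.15 names comorbidity as a potential effect modifier, so a reader needs to know which of these the trial was sized for.

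**Working it through.** **Inputs, all from section 2.17.** Control failure is 0.40 (with comorbidity) and 0.20 (without). Intervention failure as printed is 0.10 and 0.20. There are n = 73 in each of four cells, and the level is 5%. The described alternative is a joint test of the intervention and interaction terms given comorbidity, with 2 degrees of freedom. The section does not say whether the chi-square is Wald or likelihood ratio, so both are shown.

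**Step 1: relative risks.**
- As printed: 0.10/0.40 = 0.25 with comorbidity; 0.20/0.20 = 1.0 without.
- Exchanged: 0.20/0.40 = 0.5 with comorbidity; 0.10/0.20 = 0.5 without.

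**Step 2: power in closed form.** In this model the 2-df likelihood-ratio statistic is the sum of the two stratum statistics. Its approximate noncentrality is λ = 2n(D₁ + D₂). For each stratum, D = Σ [p ln(p/m) + (1 − p) ln((1 − p)/(1 − m))], summed over the two groups, where m is their mean failure rate.

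- As printed, with comorbidity (m = 0.25): D₁ = 0.4 ln(0.4/0.25) + 0.6 ln(0.6/0.75) + 0.1 ln(0.1/0.25) + 0.9 ln(0.9/0.75) = 0.1266. Without comorbidity, D₂ = 0. So λ = 146 × 0.1266 = 18.5.
- Exchanged, with comorbidity (0.4 v 0.2, m = 0.30): D₁ = 0.0483. Without comorbidity (0.2 v 0.1, m = 0.15): D₂ = 0.0199. So λ = 146 × 0.0682 = 9.96.

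The 5% critical value on 2 df is 5.99, and 80% power needs λ = 9.63. The power is therefore about 98% as printed and about 81% exchanged. The cell size for 80% is 73 × 9.63/18.48 ≈ 38 as printed and 73 × 9.63/9.96 ≈ 71 exchanged.

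**Step 3: power by simulation of the described test.** At least 20,000 runs were made per scenario. Under the null the 2-df test rejected in about 5% of runs.

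| Intervention failure (with / without comorbidity) | Power at 73 per cell, likelihood ratio | Power at 73 per cell, Wald | Cells reach 80% at |
|---|---|---|---|
| 10% / 20%, as printed | 98% | 98% | about 36 (LR) to 40 (Wald) |
| 20% / 10%, exchanged | 82% | 81% | about 70 (LR) to 72 (Wald) |

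As printed, the total needed would be 4 × 36 = 144 to 4 × 40 = 160, about half of 292. The exchanged values reproduce the plan's own figure.

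**Step 4: could another test at the 5% level explain 80% with the printed values?** At 73 per cell the printed values give:
- interaction alone: 84% to 85%
- intervention effect, adjusted or marginal: 87% to 89%
- 3-df test of the whole model: 97%

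None is within 2 points of 80%.

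**Step 5: what each reading says about the interaction.** The interaction test alone has about 85% power as printed and about 6% with the figures exchanged.

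**The case against.** The strongest reply is that the relative risk is given once and is not said to hold within each stratum. With equal cells the printed values average (10 + 20)/2 = 15% against (40 + 20)/2 = 30%, an overall relative risk of exactly 0.5. That is true, so the relative-risk sentence taken alone does not prove an error. It does not rescue the paragraph, though. The stratum without comorbidity still shows no reduction, and power is still 87% to 89% for the overall intervention effect and 98% for the described joint test.

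Second, the exchange is an inference, because the code is not shown. Other routes to a figure near 80% exist: a single marginal test of intervention at a halved level of 2.5% gives about 81% with either order. But the section states a 5% level and a joint alternative, so that route contradicts the text.

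Third, 292 is not too small on either reading. It is about right with the exchanged figures and more than enough for the described test with the printed ones. This stands, and it limits the practical harm: the defect lies in the justification, not in the number to be recruited.

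**Conclusion.** The concern holds. The printed assumptions contradict the claimed reduction, do not give a relative risk of 0.5 in either stratum, and yield about 98% power at 73 per cell where "approximately 80% statistical power" is stated. Exchanging the two intervention figures resolves all three at once and gives 81% to 82%. The most probable explanation is a transposition in the sentence, with 292 correctly derived from 20% and 10%.

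The power figures rest on reading the described test as a 2-df joint test with equal cells of 73. The choice between Wald and likelihood ratio does not alter the conclusion. The relative risks of 0.25 and 1.0 need no assumption beyond the order that the text itself fixes.

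**What to change.** Check the simulation code for the intervention-group values.

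- **If it used 20% with comorbidity and 10% without:** put the two figures in that order. State that the relative risk of 0.5 applies in each stratum, and keep 73 per cell and 292 in total. It would be fair to add that under this assumption the interaction test alone has only about 6% power, so that nobody reads the trial as sized to detect effect modification.
- **If it used 10% and 20% as printed:** remove the claim that both proportions fall. Give relative risks of 0.25 and 1.0 by stratum (0.5 only as an overall average), and restate the power as about 98% for the described test.

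In either case, say whether the chi-square is Wald or likelihood ratio, so that the figure can be reproduced. The cost is a code check, a re-run of the existing simulation and one corrected sentence, or a restated relative risk and power. Enrolment does not change.

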**Method:**

In a RCT following a feasibility study (n=50), patients will be randomly assigned in a 1:1 ratio to receive either usual care (n=150) or usual care plus an e-based PE program at home (n=150). The exercise program consists of resistance training with resistance bands targeting the lower extremities. The sessions will enable participants to engage in group exercises from their homes, supervised online by physiotherapists, two 60-minute sessions per week for 6 months (24 weeks and 48 sessions). The primary endpoint is change of walking capacity using the 6-minutes’ walk test. Secondary endpoints include “no evidence of disease activity” (NEDA)-3 scale, measures of quality of life and fatigue as well as levels of neurofilament light chain in blood and cerebrospinal fluid.

Results of the feasibility study: Fifty individuals were eligible and randomized to an intervention group (n = 23) or to a usual care control group (n = 27). A total of 24 sessions were conducted for three months in groups of 6, supervised by the physiotherapist. In the intervention group, two pwMS did not begin the PE program due to occupational constraints with a resulting recruitment rate of 91.3% (21/23). Of the remaining 21 individuals, 16 (76.2%) completed the follow-up assessments with a mean attendance of 15.2 (range 6-22) sessions per participant, corresponding to a 63% adherence rate. No intervention‐related adverse events were reported.

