### Results of the feasibility study

2.20

Participants in the intervention group at baseline received education on using the online platform and had an individual virtual session with the physiotherapist to test the setup. All 24 sessions were conducted within three months in virtual groups of 6 participants, supervised by a trained physiotherapist. Continuous communication and supervision were provided by the physiotherapist.

In the digital PE group, 23 participants were enrolled, two did not begin the PE program due to occupational constraints, yielding a recruitment rate of 91.3% (21/23). Of these, 16/21 (76.2%) completed the follow-up assessments, five participants discontinued participation due to competing personal demands including spousal illness and familial health burdens (n=3) as well as participant-specific factors such as auditory deficits (n=1), and occupational constraints (n=1). No intervention‐related adverse events (AEs) were reported.

Adherence rate and compliance: the 16 participants who completed follow-up collectively attended 243 sessions. This results in a mean attendance of 15.2 (range 6-22) sessions per participant out of the planned 24 sessions, corresponding to a 63.33% adherence rate.

Baseline characteristics of the intervention group (n = 21/23) showed a mean age of 58.7 years (SD 11.3), 42.8% of participants had ≥1 comorbidity, and the median EDSS was 3.5 (IQR 3.75).

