## Discussion

3

This protocol describes a prospective RCT study designed with longitudinal follow-up of pwMS with and without comorbidities, utilizing a standardized comorbidity-focused algorithm to explore the efficacy of e-based PE interventions in addition to usual care on clinical and paraclinical outcomes. The methodology includes standardized data collection on comorbid conditions such as recording the date of diagnosis, verifying diagnoses, assessing disease duration, a clinical examination and assessment of comorbidities, determination of functional capacity by 6MWT, and evaluation of cardiorespiratory fitness by the Ekblom-Bak test, a sub-maximal cycle ergometer assessment, estimating the maximal oxygen uptake (VO2-max). Finally, pwMS will complete a range of patient-reported health status questionnaires. at baseline and end of study. We have tested this structured approach in a feasibility study to enhance the rigor of the main RCT and results support to proceed to RCT. Fifty pwMS were eligible and randomized into the usual care control group or to the intervention group with an overall recruitment rate of 91.3%. In the intervention group 76.2% completed the follow-up assessments and had complete outcome data. Determination of functional capacity and evaluation of cardiorespiratory fitness were performed at baseline and at the end of the study. No intervention‐related SAEs were reported. Tracked adherence using a diary or logbook as the participants logged into the computer for the exercise session showed a 63.3% adherence rate. Attendance and progress were rigorously monitored, with physiotherapists recording each session’s attendance and participants logging their exercise progression into personal diaries. This dual tracking system ensured a detailed overview of engagement and advancements. Moreover, we used strategic communication techniques to boost participation and adherence. Using SMS reminders and phone calls, we motivated participants and provided them with timely notifications about upcoming sessions, significantly enhancing engagement and consistency in participation. Despite this thorough approach, the feasibility study had a 23.8% (5/21) drop-out, the most common reasons being lack of time and support due to illness in the family and occupational constraints. These challenges underscore the need for enhanced flexibility of scheduling and tailored support such as recording of the PE programme for later performance. In the feasibility study the progression models showed statistically significant upward trends, indicating consistent weekly increases. The progression models may improve functional capacity in assessment in the future RCT study.

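### The sample size section allows 2.7% loss, the feasibility study's exercise arm lost 24% in half the time, and on the reading that reproduces 80% the planned 300 give about 64–77% power at 24–30% loss

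*Protocol article*

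**What the plan says.** Section 2.17 (Sample size calculation) plans a binary outcome, achieving or not achieving a clinically meaningful improvement on the 6-minute walk test (6MWT), in four cells defined by arm and comorbidity. It tests for a main effect or an interaction "using a chi-square test derived from the logistic regression model". It concludes that "a total of 73 participants per combination of intervention and comorbidity status (i.e., 292 participants in total) would be required" to reach "approximately 80% statistical power at a 5% significance level". No allowance for missing outcomes is mentioned.

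The failure rates assumed for the control arm are that "40% of participants with comorbidity and 20% without comorbidity would fail to achieve a clinically meaningful improvement in 6MWT". For the intervention arm, "these proportions were expected to be reduced to 10% and 20%, respectively". The section then describes the effect as a relative risk of 0.5.

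The abstract plans 150 participants on usual care and 150 on "usual care plus an e-based PE program at home (n=150"). Section 2.2 plans 150 with and 150 without comorbidity, so about 75 per cell.

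On retention, section 2.20 reports for the feasibility study's exercise arm that "16/21 (76.2%) completed the follow-up assessments, five participants discontinued participation". Two more of the 23 allocated to exercise never began. The Discussion states that "the feasibility study had a 23.8% (5/21) drop-out". That programme had 24 sessions in three months; the main trial's has 48 sessions in six. Control-arm retention is not reported.

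**The concern.** The number required for the stated power and the number to be randomised are almost the same, so the calculation works only if nearly everyone supplies the outcome. The article also reports that about a quarter of exercise starters were not assessed at the end of a programme half as long. It says the feasibility results support going ahead, but the retention result does not enter the sample size.

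At stake is whether the stated 80% describes the trial that will be run. If it does not, readers will overrate what a non-significant result means.

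**Working it through.** **Margin for loss.** 4 × 73 = 292 required and 2 × 150 = 300 planned. 1 − 292/300 = 8/300 = 2.7%.

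**Loss in the feasibility study, exercise arm.**
- Starters: 5/21 = 23.8%, exact 95% CI 8.2–47.2%.
- All randomised, if the two non-starters were also not assessed: (2 + 5)/23 = 7/23 = 30.4%, exact 95% CI 13.2–52.9%.
- Even the lower limit of 8.2% is about three times the 2.7% margin.

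**Reproducing the plan's figure.** I read the alternative hypothesis (main effect or interaction) as a joint 2-df test. With comorbidity in the model, the Wald statistic is the sum over the two comorbidity strata of (log odds ratio)²/variance, compared with the χ² critical value on 2 df, 5.99. At 73 per cell with rates 40→20% and 20→10%:
- With comorbidity: log OR = ln[(0.4/0.6)/(0.2/0.8)] = 0.981; variance = (1/0.4 + 1/0.6 + 1/0.2 + 1/0.8)/73 = 10.417/73 = 0.1427; contribution 0.981²/0.1427 = 6.74.
- Without comorbidity: log OR = ln[(0.2/0.8)/(0.1/0.9)] = 0.811; variance = (1/0.2 + 1/0.8 + 1/0.1 + 1/0.9)/73 = 17.361/73 = 0.2378; contribution 0.811²/0.2378 = 2.77.
- Non-centrality 6.74 + 2.77 = 9.51, which gives 79% power by the large-sample approximation.

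Simulation (400,000 runs) gives 80.6% (Wald), 81.7% (score) and 82.2% (likelihood ratio), so the stated 80% is reproduced.

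**Rates in the printed order (40→10%, 20→20%).** The relative risks are 0.10/0.40 = 0.25 and 0.20/0.20 = 1.0, not 0.5. The joint test then has about 98% power at 73 per cell and needs only about 36 per cell for 80%. Other tests do not recover 80% at 73 per cell: a 1-df main-effect test gives about 88% under either order, and the interaction test alone gives 84.5% under the printed order and 6% under relative risk 0.5.

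**Power with 300 randomised (75 per cell), after loss.** Expected completers per cell are 75 × 16/21 ≈ 57 and 75 × 16/23 ≈ 52. Ranges run from the lowest to the highest of the Wald, score and likelihood-ratio versions.

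| Loss | Control / exercise per cell | Complete | Power, 40→20% and 20→10% | Power, rates as printed |
|---|---|---|---|---|
| 23.8%, exercise arm only | 75 / 57 | 264 | 74–77% | 96–97% |
| 30.4%, exercise arm only | 75 / 52 | 254 | 71–75% | 94–96% |
| 23.8%, both arms | 57 / 57 | 228 | 69–72% | 93–95% |
| 30.4%, both arms | 52 / 52 | 208 | 64–67% | 91–93% |

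For comparison, an assumed 15% loss in both arms (64 per cell, 256 complete) gives 75–77%.

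**The case against.** **The rates are a repair.** Section 2.17 does not print 40→20% and 20→10%. On the rates it does print, power stays above 90% after these losses and there is no shortfall. This stands as a condition on the conclusion. It does not rescue the stated figure, because the printed order contradicts the section's own relative risk and does not give 80% at 292.

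**The loss estimate is thin.** It comes from 21 to 23 people in one arm, its interval is wide, and the article draws lessons from the drop-out, such as flexible scheduling and recorded sessions. That is why I show a range. The lower confidence limit is still well above 2.7%.

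**Not starting is not the same as not being assessed.** The article gives follow-up as 16 of 21 and does not say whether the two non-starters were tested. Under intention to treat they could still supply a 6MWT. So 23.8% is the documented loss and 30.4% an upper case.

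**The efficacy analysis is not the responder test.** Section 2.18 describes models for repeated measurements under missing at random, and the 6MWT is also taken at 3 months. Some people without a 6-month value would still contribute. How much this recovers is unknown, since no power is given for that analysis.

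**Stronger readings that are not supported.** A reader might infer that the 3-month loss simply repeats over months 3 to 6, leaving about half the sample: 21/23 × (16/21)² = 53%. Nothing in the article supports a constant loss rate, least of all in a control arm with no data. Squaring 16/23 would also count the two non-starters twice. Nor can one conclude that loss will be concentrated in the exercise arm, because control-arm retention is not reported.

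**Conclusion.** The point holds as a should-fix. The 80% in section 2.17 depends on at most 2.7% missing outcomes, and the trial's own evidence points to a much larger loss. If that loss recurs, power is about 74–77% (24%) or 71–75% (30%) with loss in the exercise arm only, and 69–72% or 64–67% with equal loss in both. The shortfall is moderate, but at these losses it is present even if the control arm loses nobody.

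This rests on four assumptions: failure rates of 40→20% and 20→10%; a joint 2-df test; a complete-case binary outcome at 6 months; and feasibility loss carried over unchanged to a programme twice as long. A reader might infer that the trial is underpowered whatever the rates. The document does not support that, because with the rates as printed power would be 91–97% after the same losses. Until that contradiction is settled, no single power figure for this design can be relied on.

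**What to change.** In section 2.17:

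1. Reconcile the intervention failure rates with the relative risk of 0.5, since every power figure depends on them.
2. State an explicit loss assumption based on the feasibility data from both arms. Report how many control participants were followed up and whether the two non-starters were assessed.
3. Restate power, or the effect detectable at 80% power, for the number expected to have a 6-month 6MWT. If the rates are confirmed as 40→20% and 20→10%, the power to report at 24–30% loss is about 64–77%, depending on whether one or both arms lose participants.
4. Say that these figures are for the binary responder test, and that the repeated-measures model may recover some information.

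The cost is a less favourable stated power under the reconciled rates. The design, sample and analysis do not change. Enlarging the trial is not required; keeping 292 complete outcomes would take 292 × 21/16 ≈ 384 to 292 × 23/16 ≈ 420 randomised.

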### Statistical analysis

2.18

All data generated and collected during the project will undergo comprehensive statistical analysis using both traditional and advanced modeling techniques. The analyses will follow the intention-to-treat (ITT) principle as the primary analytic strategy. A per-protocol (PP) analysis will be conducted as a secondary approach, restricted to participants in the intervention group who meet the following criteria: (1) attendance of at least 75% of the prescribed exercise sessions, (2) completion of at least one follow-up assessment (e.g., at 6 months), and (3) submission of required self-report data such as exercise diaries and PROMs.

To evaluate the efficacy of the PE intervention, longitudinal changes in outcomes such as exercise capacity, functional abilities, and patient-reported measures will be analyzed using a multivariable regression model.

These models account for repeated measurements within individuals over time and are well suited to the handling of missing data under a missing-at-random assumption.

In parallel, changes in clinical disease biomarkers and standard clinical outcomes (e.g. EDSS, relapse rate) will also be examined using mixed-effects models for both within-group and between-group comparisons. Particular attention will be given to biomarkers that reflect MS activity or progression (e.g., serum GFAP, NfL), with adjustment for relevant covariates such as age, sex, and disease duration.

Key statistical analyses will include:

Association analyses, where logistic regression models will be used to assess the relationships between clinical outcomes and explanatory variables such as comorbidity status, age, and sex, including testing for potential interaction effects.Correlation analyses, where Pearson or Spearman correlation coefficients will be estimated to explore associations between multiple clinical endpoints, aiding in the interpretation of the multidimensional impact of MS.Predictive modeling of disease progression, which will be pursued as part of a follow-up analysis. We aim to construct models to predict MS progression by integrating disease biomarkers and vascular comorbidity risk factors. To this end, lasso logistic regression models will be employed, and model performance will be assessed using Area Under the Curve (AUC) metrics.

During the current study phase, preliminary steps will focus on feature selection and initial model training, which will lay the groundwork for more comprehensive models in future phases. Collectively, these statistical approaches are intended to provide a robust, multidimensional understanding of MS progression and the role of PE interventions and comorbidities in shaping long-term outcomes.

In the feasibility study for the progression model for PE level and band intensity a linear mixed-effects model was fitted separately for PE level (1–3) and for band code (1 = yellow…6 = gold), each with week (1–12) as the sole fixed effect and with random intercepts and random slopes by patient to account for individual baselines and progression rates.

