### Adherence measurement and motivation strategies

2.8

Attendance is recorded by the physiotherapist after each session. Additionally, patients are required to log their exercise progression in personal diaries, ensuring comprehensive tracking of their engagement and progress. We will employ strategic communication methods to bolster participation and adherence, including SMS reminders and phone calls. These reminders serve not only to motivate but also to provide timely prompts for upcoming sessions, thereby aiming to enhance overall engagement and consistency in participation.

Adherence to the intervention will be assessed at the 6-month follow-up as the number of exercise sessions attended out of the total number of sessions available. Satisfactory adherence will be attained when completing 36 out of 48 sessions (75%).

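### The per-protocol analysis filters only the intervention arm, so it has either no comparator or a comparison that randomisation no longer protects

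*Protocol article*

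**What the plan says.** Section 2.18 of the protocol article sets the hierarchy: "The analyses will follow the intention-to-treat (ITT) principle as the primary analytic strategy". The per-protocol analysis is the secondary approach, and its population is "restricted to participants in the intervention group who meet the following criteria: (1) attendance of at least 75% of the prescribed exercise sessions". The second criterion is "completion of at least one follow-up assessment (e.g., at 6 months", with 6 months given only as an example. The third is "submission of required self-report data such as exercise diaries and PROMs". The section states no criterion for usual-care participants, no comparator for this set and no adjustment for the selection.

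Section 2.8 defines satisfactory adherence as 36 of 48 sessions, which is the same 75%. Table 2 schedules the 6-minute walk test (6MWT) and the patient-reported outcomes at baseline and at 3, 6, 12 and 24 months, with no distinction by arm. The abstract plans 150 patients per arm. Section 2.20 reports, for the 16 exercise-arm completers in the feasibility study, a "mean attendance of 15.2 (range 6-22) sessions per participant out of the planned 24 sessions".

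**The concern.** A per-protocol analysis is usually read as an estimate of what the treatment does, compared with control, in people who take it as planned. That needs a control group, and the control group has to be comparable. The definition in section 2.18 secures neither.

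Attendance and exercise diaries exist only in the intervention arm, so some asymmetry is unavoidable. Follow-up visits and patient-reported outcomes exist in both arms, yet they are required of one. An analysis plan built on this text would produce either a description of one arm or a comparison of a filtered arm with an unfiltered one. Because it is called a secondary approach to efficacy, a favourable result could be reported as support for the programme when part or all of it reflects who attends.

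**Working it through.** **1. The plan's own figures.** The threshold is 36/48 = 0.75. Feasibility attendance is 243/16 = 15.19 sessions per completer, and 15.19/24 = 63.3%. Both reproduce. The 63.3% describes the 16 completers, not all 23 randomised to exercise.

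**2. Which criteria could apply to which arm.**

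| Criterion (section 2.18) | Intervention | Usual care |
|---|---|---|
| At least 75% attendance | Recorded after each session (2.8) | No counterpart |
| At least one follow-up | Table 2 | Table 2, same visits |
| Exercise diary | 2.8, Table 1 | None |
| Patient-reported outcomes | Table 2 | Table 2, same schedule |

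The daily diary kept by both arms (section 2.12) records adverse events. It is not the exercise diary and cannot stand in for it.

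**3. The follow-up criterion and the endpoint.** At two sessions a week, 36 sessions take at least 36/2 = 18 weeks. Anyone meeting the attendance criterion is therefore past the 3-month visit, and that visit alone can satisfy the follow-up criterion. So can a 12- or 24-month visit. A patient can qualify with no 6-month walk test, although section 2.12 calls 6 months the primary endpoint and section 2.15 frames the outcome as change to the end of the programme.

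**4. How many might qualify.** Inputs from section 2.20: 16 completers, 243 sessions in total, range 6 to 22. The pilot equivalent of 75% is 18 of 24. Let k completers reach 18 or more.

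- Lower limit: someone attended 22, so k is at least 1. With k = 1, the largest possible total is 22 + 6 + 14 × 17 = 266, which is at least 243, so k = 1 is possible.
- Upper limit: with k = 11, the smallest possible total is 22 + 10 × 18 + 5 × 6 = 232, which does not exceed 243. With k = 12 it is 22 + 11 × 18 + 4 × 6 = 244, which does. So k is at most 11.

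If none of the 7 non-completers qualified, the share of those randomised lies between 1/23 = 4% and 11/23 = 48%. Carried over to 150 patients, that is about 7 to 72.

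A narrower figure needs an assumed shape. With a normal distribution and an SD of 3 to 5 sessions (not reported), P(X ≥ 17.5) is 0.22 to 0.32. Multiplying by 16/23 gives 15% to 23%, or about 23 to 34 of 150. This illustrates the point and is not a result of the documents.

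**5. What the loose reading could do.** Assume no true effect, a correlation rho between attendance and change in 6MWT, and a top fraction f of the arm compared with 150 unselected controls. The expected difference in SD units is rho × φ(t)/f, where t is the upper-f normal quantile.

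- rho = 0.1, f = 0.5: 0.1 × 0.399/0.5 = 0.08 SD; nominal 5% error becomes about 9%.
- rho = 0.3, f = 0.2: 0.3 × 0.280/0.2 = 0.42 SD; nominal 5% error becomes about 58%.

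Both rho and f are assumptions. A negative rho gives the mirror image. This shows that the mechanism can matter, not that it will.

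**The case against.** The strongest reply is that little depends on this analysis. Intention-to-treat is explicitly primary, no decision rule or sample size is tied to the per-protocol set, and the handling of a secondary population is often left to an analysis plan, which is not shown here. The limit on importance stands. The appeal to an unseen plan does not, because the article states the population and states it in a form that needs correcting.

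The follow-up criterion also has a defence. Section 2.18 describes models for repeated measurements under a missing-at-random assumption, so a patient without a 6-month value can still contribute. That is fair, and the number of such patients is unknown. Still, a set meant to represent completion of the programme should contain its end-of-programme measurement.

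Four stronger readings are tempting, and the documents do not support them:

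- **That the set will be a small minority of the arm.** The pilot totals allow up to 48% of those randomised.
- **That the 75% cut is wrong because pilot completers averaged 63%.** The cut defines adequate exposure and does not forecast mean attendance.
- **That the bias favours exercise.** The discussion (section 3) says fatigue can hinder adherence and that mobility problems complicate participation, which makes that direction conceivable. But the endpoint is change in 6MWT, and the reasons recorded in section 2.20 for not starting or stopping were mainly work and family circumstances. The sign is not shown.
- **That an instrumental-variable estimate must replace the analysis.** It has debatable assumptions of its own: participants are unblinded, and the intervention arm also receives in-person instruction, a one-to-one virtual session and reminders.

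**Conclusion.** The point holds as a defect in how a secondary analysis is defined. As written, the per-protocol set either cannot estimate an effect against usual care or sets self-selected attenders against unselected controls. Nothing elsewhere in the article supplies a comparator. The follow-up criterion additionally admits patients without the 6-month walk test.

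The direction and size of any bias cannot be determined from the documents. The qualifying share is anywhere from 4% to 48% of the arm (about 7 to 72 of 150), assuming that no pilot drop-out qualified and that attendance in a 24-session, 3-month pilot carries over to a 48-session, 6-month trial.

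A reader might infer that the trial's main conclusion is compromised. It is not, because the primary intention-to-treat analysis does not use this set. The text should be corrected before any per-protocol result is read as efficacy.

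**What to change.** Reword the per-protocol paragraph in section 2.18, and carry it into the analysis plan, so that it:

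1. names the usual-care arm as comparator;
2. applies the follow-up and patient-reported-outcome criteria to both arms, and keeps attendance and exercise diaries for the intervention arm only;
3. requires the 6-month 6MWT;
4. adjusts for baseline 6MWT and the stratification factors (comorbidity status, age, sex, EDSS);
5. labels the result descriptive and not evidence of efficacy.

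These steps reduce the imbalance but do not restore randomisation, because attendance still selects within one arm. Hence the label.

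If an adherence-related effect is wanted, add a complier-average estimate in all randomised patients beside the intention-to-treat result, with randomised arm as the instrument and the attendance already recorded as the exposure.

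The cost is wording only, with no new data. The complier-average estimate will have a wider interval. It assumes that assignment acts only through attendance and, if the number of sessions is the exposure, that the effect per session is linear. Both assumptions should be stated with the result.
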